#### Exclusion criteria

Children with food allergies or food intolerances, with uncorrected severe hearing impairment, whose parents do not give their informed consent, with a poor understanding of oral and written language, or who have previously been involved in the Healthy Breakfast Programme, will be excluded.

#### Loss to follow-up

Withdrawals will be recorded when parents or tutors rescind consent for a pupil to continue. Few withdrawals may be expected since both proposed interventions are one-off experiences and are associated with no adverse effects. Further, the duration of the trial is only 6 months. Those children who do not complete the required questionnaires 7 days and 6 months after the interventions will also be considered lost to follow-up. Such problems can be minimised since the collaboration of the participating centres’ staff can be counted upon; indeed, the class teachers will be charged with passing out these questionnaires. Children will be weighed and measured on the day of the interventions and 6 months later. However, the nurse hired for the project will also go to the schools 3 days after the second measurement to measure those children who were not present, thus reducing loss to follow-up.

### Intervention groups

•Healthy Breakfast group (Group HB)

This group will receive a Healthy Breakfast class. The activity will be held in school hours in the school dining hall, and will take 1 h to complete. A maximum of 50 children per turn will be admitted. The session will be structured as follows:

•
*Preparation of the dining hall for the activity (10 min).* This involves putting out a table mat, a cup, a plate and two slices of bread per child, a 1 L bottle of milk for every four children, and a 1 L bottle of virgin olive oil for every 12 children. The dining hall will be set up before the children come in.

•Introduction to the speakers by a teacher (5 min).

•
*Participatory lesson (20 min)*. This will be supported by a Power Point presentation based on the NAOS strategy with the following basic contents: the ideal number of daily meals, the importance of breakfast for the day’s activity, leaving sufficient time for breakfast, the basic components of a healthy breakfast, the role of cereals at breakfast, the role of dairy products at breakfast, the role of fruits at breakfast, the importance of exercise for cardiovascular health, and the outcome of unhealthy habits (sedentary lifestyle).

•
*Healthy breakfast time (25 min)*. The children will consume the milk, the piece of fruit and the slices of bread with oil.

#### Farewell and closing

The children will be invited to take home the table mat and the cup they used; these will be inscribed with the slogan: “I am a Heartsaver”. This will serve as a reminder of the activity. A pamphlet on the NAOS strategy will also be provided for them to take home.

•Music concert group (Group MC)

The members of Group MC will attend an educational, participatory, music concert that delivers the same health messages imparted to Group HB, but through the vehicle of music and storytelling. The concert will take place within school hours in the school auditorium or gym over a period of 1 h. A maximum of 50 children will be present per turn. The session will be structured as follows.

•
*Preparation of the auditorium/gymnasium for the activity (10 min).* This involves putting out the chairs with a concert programme on each, the arrangement of music stands for four musicians and a storyteller on the stage, and setting up a NAOS strategy Power Point presentation used to project reinforcing images (e.g., children eating healthily, running or playing etc.). All these will be arranged before the children come in.

•Introduction of the musicians by the storyteller (5 min).

•
*Beginning of the concert*. The concert, which involves five songs and a story based on the NAOS strategy goals (outlined in Appendix 1)*,* lasts 40 min. Children will be asked to clap, raise their hands at appropriate moments, and to become ‘Heartsavers’.

•
*Farewell and closing*. The children will be invited to take the concert programme home as a bookmark, along with a cup, both inscribed with: “I am a Heartsaver”. These should serve as reminders of the activity. A pamphlet on the NAOS strategy will also be provided for them to take home.

### Study stages and variables measured

The variables measured will be:

•
*Demographic variables*. Age, date of birth and gender information will be collected from all participating children.

•
*Knowledge variables*. The children’s knowledge of obesity-prevention/good cardiovascular health practices will be measured via a true/false multiple choice questionnaire composed of 10 questions adapted from the 10 messages of the NAOS strategy. These questions were designed by educators and teachers of the Healthy Breakfast Programme. This questionnaire will be the same for the children in both Groups HB and MC, and will be answered in the classroom the day before the interventions, and then again 7 days and 6 months later. The outcome variable measured will be the number of correct answers.

•
*Attitude variables*. These will be measured using a set of 10 cards, each with different exercises, in which students must chose the healthy attitudes from the variety offered. This activity, to be undertaken by all children in the study, will be performed during regular school time 5 school days prior to the interventions and then 6 months after the interventions. The outcome variable recorded will be the number of correct answers.

•
*Weight change*. Reductions in obesity will be recorded in both Group MC and HB. Weight and height measurement will be measured, using a single, calibrated portable scale and a portable stadiometer, by a single trained nurse hired for the project. All children will be so measured on the day of the interventions and again 6 months later. The outcome variable recorded will be the percentage of children who reduced their BMI percentile out of those children considered overweight/obese prior to the interventions.

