**Methods/design:**

This study will involve a cluster-randomised trial with blinded assessment. The study subjects will be children aged 7–8 years of both sexes attending public primary schools in the Madrid Region. The participating schools (n=30) will be randomly assigned to one of two groups: 1) Group MC, in which the children will attend a music concert that delivers obesity-preventing/cardiovascular health messages, or 2) Group HB, in which the children will attend a participatory class providing the same information but involving the description and making of a healthy breakfast. The main outcome measured will be the increase in the number of correct answers scored on a knowledge questionnaire and in an attitudes test administered before and after the above interventions*.* The secondary outcome recorded will be the reduction in BMI percentile among children deemed overweight/obese prior to the interventions. The required sample size (number of children) was calculated for a comparison of proportions with an α of 0.05 and a β of 0.20, assuming that the Group MC subjects would show values for the measured variables at least 10% higher than those recorded for the subjects of Group HB. Corrections were made for the design effect and assuming a loss to follow-up of 10%. The maximum sample size required will be 2107 children. Data will be analysed using summary measurements for each cluster, both for making estimates and for hypothesis testing. All analyses will be made on an intention-to-treat basis.

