### Aims

The main aim of the proposed trial is to determine whether a health promotion strategy involving an educational music concert for schoolchildren aged 7–8 years improves knowledge of, and attitudes towards, obesity prevention/good cardiovascular health habits (as suggested by the NAOS strategy) better than a health promotion strategy involving an Healthy Breakfast.

The secondary aim is to compare the two interventions, at 6 months, in terms of the reduction achieved in BMI percentile by children who are overweight/obese prior to the start of the study.

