### Assessment of efficacy

The efficacy of the different strategies will be measured using the following variables.

•
*Recent knowledge acquisition*. Difference in the percentage of correct answers recorded for the first knowledge questionnaire (prior to the interventions) and the second knowledge questionnaire (7 days later) (Figure 1). Marking will be performed by two trained teachers (members of the research team), both of whom will be blinded to the groups to which the children belonged.

•
*Memory of the knowledge acquired*. Difference in the percentage of correct answers between the first knowledge questionnaire (prior to the interventions) and the third knowledge questionnaire 6 months later (Figure 1). Marking will be performed by the same two teachers, both of whom will be blinded to the groups to which the children belonged.

•
*Change in attitudes*. Difference in the percentage of ‘right attitudes’ recorded in the attitude test conducted 7 days before the interventions and 6 months after (Figure 1). The assessment of these attitudes will be undertaken by the same two teachers, both of whom will be blinded to the groups to which the children belonged.

•
*Reduction in obesity*. Change in BMI percentiles of children originally classified as overweight/obese. The evaluation will be performed by a paediatrician (a project team member), who will be blinded to the groups to which the children belonged.

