### Statistical analysis

Primary analysis will be made on an intention-to-treat basis. The stages of the analysis will be:

1. *Descriptive analysis*. Quantitative variables will be described by their measures of central tendency, i.e., the mean or median (in the case of asymmetric distributions) plus the respective standard deviation or interquartile range. Qualitative variables will be described in terms of ratios.

2. *Comparison of the baseline characteristics of both groups*. The characteristics of the children in both trial arms, and of their families and their schools, will be described and compared. Special attention will be paid to variables that may influence the results. Parametric tests will be used to verify the effectiveness of randomisation. Potential confounders will be identified and appropriate adjustments made in the analysis of the primary efficacy variables.

3. *Primary efficacy analysis*. Relative risk, absolute risk reduction, and the relative reduction of risk will be used as measures of the strength of associations. The null hypothesis is that there are no differences between the two interventions in terms of improving the knowledge and skills associated with obesity prevention/good cardiovascular health habits. Multivariate analyses will be performed taking into account the type of design employed via the use of generalized linear models or multilevel models. The 95% confidence interval will be calculated for all estimates. A sensitivity analysis will be performed, assigning values supportive of the null hypothesis to all missing data.

All analyses will be made using PAWS and/or STATA software.

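### The only named secondary outcome is given both as the percentage of children with any fall in BMI percentile and as the amount of change; the two forms are not reconciled, and the any-fall form is the less precise one.

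*Protocol article*

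**What the plan says.** Four places in the protocol article define the BMI outcome.

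- **Study stages and variables measured (weight change):** "The outcome variable recorded will be the percentage of children who reduced their BMI percentile", with children overweight or obese at baseline as the denominator. This is a yes/no result per child, and no minimum fall is set.
- **Assessment of efficacy (reduction in obesity):** "Change in BMI percentiles of children originally classified as overweight/obese". This is a change, with no responder rule.
- **Aims:** the arms are compared at 6 months on "the reduction achieved in BMI percentile by children who are overweight/obese prior to the start of the study".
- **Abstract, methods/design:** "The secondary outcome recorded will be the reduction in BMI percentile among children deemed overweight/obese prior to the interventions".

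The statistical analysis section names effect measures, "Relative risk, absolute risk reduction, and the relative reduction of risk will be used as measures of the strength of associations", but under the primary efficacy analysis. It gives no summary measure for BMI. The sample size section concerns knowledge only, so the BMI outcome has no stated power, SD or expected proportion falling.

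**The concern.** A percentage of children who fell and an amount of change are different estimands. They need different summary measures (a risk ratio or risk difference against a difference in means), and they can disagree on which arm did better. With both in the text, the choice could be made after the data are seen.

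The any-fall form also has weaknesses of its own. A very small drop counts the same as a large one. A child can count as a success under a bullet about reduced obesity and still be obese. Cutting a measured change at zero loses precision, in a comparison already confined to a minority of the children. Finally, the children are selected for a high value at one measurement, so many would show a fall without any intervention effect.

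**Working it through.** **1. The plan's own figure.** No figure is stated for BMI. The only one to reproduce is the knowledge calculation (40% v 50%, α 0.05, power 0.80; two-sided assumed): [1.96·√(2·0.45·0.55) + 0.842·√(0.40·0.60 + 0.50·0.50)]² / 0.10² ≈ 388 per arm, against the stated 391. It agrees closely and does not bear on BMI.

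**2. Can the two forms rank the arms differently?** Yes. Take a normal change and, for illustration only:
- arm A, mean fall 0.20, SD 0.4: share falling Φ(0.20/0.4) = Φ(0.50) = 69%;
- arm B, mean fall 0.25, SD 0.8: share falling Φ(0.25/0.8) = Φ(0.31) = 62%.

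B has the larger mean fall, and A has more children falling.

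**3. Information kept by the any-fall cut.** For a normal variable cut so that a proportion p falls, relative efficiency is φ(z_p)² / [p(1 − p)]:
- p = 0.50: 2/π = 0.64
- p = 0.60: 0.62
- p = 0.65: 0.60

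The loss is therefore about 36–40%.

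**4. Illustrative power.**
- From the article: recruited totals 1110 and 2107 and ICCs 0.01 and 0.05 (sample size section, which pairs 1110 with 0.01 and 2107 with 0.05); 10% loss; 30 schools; 30.4% overweight or obese at ages 6–9 (background).
- Assumed: a difference of 0.25 SD, normal change, two-sided 5%, and the knowledge ICCs applied to both forms of the BMI outcome.

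Subgroup n = recruited × 0.9 × 0.304; m = n/30; design effect = 1 + (m − 1) × ICC; effective n per arm h = n/(2 × design effect). Power for the mean is Φ(0.25·√(h/2) − 1.96). For the proportion, the same shift from a 50% base gives 50.0% v Φ(0.25) = 59.9%, tested as two proportions with h per arm.

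| Recruited | ICC | n | m | Design effect | h | Mean change | Any fall |
|---|---|---|---|---|---|---|---|
| 1110 | 0.01 | 304 | 10.1 | 1.09 | 139 | 55% | 38% |
| 2107 | 0.05 | 576 | 19.2 | 1.91 | 151 | 58% | 41% |
| 2107 | 0.01 | 576 | 19.2 | 1.18 | 244 | 79% | 59% |

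The first two rows use the article's own pairings. The third applies only if the larger sample is recruited and the ICC turns out low.

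**5. Falls expected with no intervention effect.** Assume z-scores with a stable distribution and 6-month correlation r. A child at baseline z = 1.7 (assumed subgroup mean) falls on average by 1.7(1 − r), with SD √(1 − r²):
- r = 0.90: 0.170/0.436 = 0.39, Φ = 65%
- r = 0.95: 0.085/0.312 = 0.27, Φ = 61%
- r = 0.98: 0.034/0.199 = 0.17, Φ = 57%

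Simulation selecting all children above the 70th or 85th centile, over the same correlations, gives 55–64%. The overall range is about 55–65%.

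**The case against.** The strongest reply is that the forms are not incompatible. Only the variables section names a recorded outcome variable for BMI. The other three places name a concept, reduction or change, and none says mean change. A percentage who reduced can be derived from the same two measurements, and a condensed article may leave the summary statistic to a fuller document. It is right that this is an unresolved choice and not a logical impossibility. But the article does not stay silent: it fixes one form in one section and words the outcome as an amount in three others, with nothing to link them.

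A reader might infer that the any-fall percentage mostly reflects noise. The article does not support that. It gives no measurement error and no SD of change, and it limits error by "using a single, calibrated portable scale and a portable stadiometer, by a single trained nurse hired for the project". With assumed error SDs of 0.02–0.15 z per visit and true-change SDs of 0.1–0.3 z, error makes up anywhere from 1% to 82% of the variance of change.

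A reader might also infer that regression to the mean biases the result. It does not. It is expected equally in both randomised arms, and the stated aim is to compare them.

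Two further points stand. The 0.25 SD effect is assumed, and the 2/π efficiency needs a roughly normal change, which bounded percentiles near their ceiling may not show. Also, a fall/no-fall indicator is the same on percentiles and z-scores, which is a real convenience. It does not offset the loss of precision, and a continuous analysis on a named scale meets the same need.

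**Conclusion.** The concern holds as a matter of unreconciled definitions plus a less efficient recorded form. The discrepancy is in the text and needs no assumption. The any-fall cut keeps about 60–64% of the information if change is roughly normal. At 0.25 SD, that costs about 17 percentage points of power under either of the article's own pairings of sample size and ICC. These power figures are illustrations: the effect size, the normality and the ICC for BMI are all assumed.

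The 55–65% expected to fall without any effect also rests on assumed correlations. There is no untreated arm, so that rate is a reason not to read a within-arm percentage as reduced obesity; it is not a flaw in the comparison of arms. The primary outcome and the stated sample size are unaffected. The change is worth making because it is cheap and settles the outcome before the data are seen.

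**What to change.** Use one definition in the abstract, the aims, the variables section and the assessment of efficacy: the between-arm difference in change in age- and sex-standardised BMI from the day of the intervention to 6 months, among children overweight or obese at baseline. Name the scale as the z-score from the same reference as the percentiles, because percentiles compress near the ceiling. Analyse it as continuous, adjusted for the child's baseline value and allowing for school. Report the percentage with any fall by arm as a descriptive figure only, and do not label it a reduction in obesity.

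The cost is wording and one line of analysis, since weight and height are already to be measured at both times. The downside is that a mean z-score change is slightly harder for lay readers than a percentage, which is a reason to keep the percentage as description.

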### Assessment of efficacy

The efficacy of the different strategies will be measured using the following variables.

•
*Recent knowledge acquisition*. Difference in the percentage of correct answers recorded for the first knowledge questionnaire (prior to the interventions) and the second knowledge questionnaire (7 days later) (Figure 1). Marking will be performed by two trained teachers (members of the research team), both of whom will be blinded to the groups to which the children belonged.

•
*Memory of the knowledge acquired*. Difference in the percentage of correct answers between the first knowledge questionnaire (prior to the interventions) and the third knowledge questionnaire 6 months later (Figure 1). Marking will be performed by the same two teachers, both of whom will be blinded to the groups to which the children belonged.

•
*Change in attitudes*. Difference in the percentage of ‘right attitudes’ recorded in the attitude test conducted 7 days before the interventions and 6 months after (Figure 1). The assessment of these attitudes will be undertaken by the same two teachers, both of whom will be blinded to the groups to which the children belonged.

•
*Reduction in obesity*. Change in BMI percentiles of children originally classified as overweight/obese. The evaluation will be performed by a paediatrician (a project team member), who will be blinded to the groups to which the children belonged.

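### Knowledge and attitude outcomes are pre-post differences with no commitment to adjust for the baseline score, and confounders are to be identified after baseline tests of randomisation

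*Protocol article*

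**What the plan says.** Under Assessment of efficacy, recent knowledge is "Difference in the percentage of correct answers recorded for the first knowledge questionnaire (prior to the interventions) and the second knowledge questionnaire", seven days later. Retained knowledge is "Difference in the percentage of correct answers between the first knowledge questionnaire (prior to the interventions) and the third knowledge questionnaire 6 months later". Attitude change is "Difference in the percentage of ‘right attitudes’ recorded in the attitude test" before the interventions and six months after. The abstract agrees: "The main outcome measured will be the increase in the number of correct answers scored on a knowledge questionnaire and in an attitudes test".

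The baseline score is available in both arms. Under Study stages and variables measured, the knowledge questionnaire "will be answered in the classroom the day before the interventions, and then again 7 days and 6 months later", and the attitude test is also given before the interventions. The same section states "Age, date of birth and gender information will be collected from all participating children". Schools are sampled within strata of rural/urban location and socioeconomic level (Study population).

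On the main efficacy comparison, Statistical analysis, item 2, says: "Parametric tests will be used to verify the effectiveness of randomisation. Potential confounders will be identified and appropriate adjustments made in the analysis". Item 3 allows generalised linear or multilevel models that respect the design and names relative risk and absolute risk reduction, but lists no covariates. The abstract says that summary measures per cluster will be used for estimation and testing.

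**The concern.** Two choices weaken the primary comparison.

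First, an unadjusted change score fixes the coefficient on baseline at 1. Unless the true regression slope of follow-up on baseline is 1, this adds noise and over-corrects any chance difference between arms at baseline. With 30 schools, some difference in mean baseline score is to be expected. The knowledge test has ten true/false items, so children who start high have little room to gain, and a slope below 1 is plausible.

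Second, under random allocation any baseline difference arises by chance, so a significance test cannot verify the randomisation. Identifying confounders after the baseline data have been seen makes the content of the primary model depend on those data. A covariate list fixed in advance avoids this.

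At stake are precision and a primary model that is settled before the data are seen. Validity on average is not at stake.

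**Working it through.** **The plan's own figure.** The sample size compares 40% with 50% at alpha 0.05 and power 0.80. With the two-sided, pooled formula, n per arm = [1.960·√(2·0.45·0.55) + 0.842·√(0.24+0.25)]² / 0.10² ≈ 388, or 776 in all, against the stated 391 × 2 = 782. The figure reproduces to within 1%. It concerns proportions, so it contains no assumption about score variance or pre-post correlation. The article gives no figure for the precision of the score comparison.

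**Inputs.** From the article: 30 schools, ICC 0.01 to 0.05, and 1916 evaluable children, so 1916/30 ≈ 64 per school. Assumed: 15 schools per arm (the 391 × 2 implies equal allocation), equal pre and post variance s², and a pre-post correlation r, shown over a range.

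**Precision.** The variance of the effect is proportional to 2(1−r)s² for the change score and (1−r²)s² after baseline adjustment. The ratio is (1+r)/2. The last column is the power of the adjusted analysis if the change score has 80%.

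| r | adjusted / change variance | power |
|---|---|---|
| 0.3 | 0.65 | 93.5% |
| 0.5 | 0.75 | 90% |
| 0.7 | 0.85 | 86% |
| 0.8 | 0.90 | 84% |
| 0.9 | 0.95 | – |

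These are large-sample ratios. With 30 school means, estimating the slope multiplies the adjusted variance by about 1 + 1/26 = 1.04. The gain then vanishes at r of about 0.93, since (1+0.926)/2 × 27/26 = 1.

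**Simulation on school means** (15 schools per arm, 64 children each, 20,000 runs, the same r for children and schools, true difference 0.2 SD). Power, change score against adjusted:

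| ICC | r = 0.3 | r = 0.5 | r = 0.7 |
|---|---|---|---|
| 0.01 | 0.79 v 0.92 | 0.91 v 0.96 | 0.99 v 0.995 |
| 0.05 | 0.42 v 0.57 | 0.54 v 0.65 | 0.76 v 0.81 |

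With no true difference, the change score rejects in about 5% of all trials. Among trials whose baseline scores differ significantly between arms, it rejects in 12% to 24%. A rule that adjusts only after a significant baseline test recovers almost none of the power (0.546 against 0.651 for planned adjustment at ICC 0.05, r = 0.5), and its overall type I error is about 0.04.

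**Size of chance imbalance.** A school mean has variance ICC + (1−ICC)/64, which is 0.025 at ICC 0.01 and 0.065 at ICC 0.05 (in SD² units). The difference between arms has SD √(2 × variance/15), or 0.06 to 0.09 SD.

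**Level of adjustment.** Take ICC 0.05, child-level correlation 0.5 and school-effect correlation 0.95. The observed school means then correlate at R = (0.05·0.95 + 0.95·0.5/64)/0.065 ≈ 0.85. Relative to school-mean variance, the change score gives 2(1−R) = 0.31. Adjusting with the child-level slope alone gives 1 − 2·0.5·R + 0.25 = 0.40, which is worse than the change score. Adjusting for the school mean gives 1−R² = 0.28, a ratio of 0.92. For child-level correlations of 0.3 to 0.7, the school-mean ratio runs from 0.90 to 0.95.

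**The case against.** The best defence is that the efficacy section defines variables, not models. A linear model of change with baseline as covariate gives the same treatment effect as a model of follow-up with baseline as covariate, and the planned generalised linear or multilevel models could carry it. A condensed article may also leave its covariate list to a fuller document. This stands in part: the article does not exclude baseline adjustment. It does not commit to it either, and the tests of randomisation and the later confounder search are stated plans, not omissions.

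Three stronger readings are tempting and are not supported.

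- *Covariates are selected by p-value.* The article says "Parametric tests will be used to verify the effectiveness of randomisation" and then, in a separate sentence, that confounders will be identified. It gives no p-value rule, and the preceding sentence points to variables that may affect the results.
- *Children will be tested as if independent.* Item 2 does not mention clustering, but the abstract plans cluster summaries for hypothesis testing, so a false-alarm rate built on independent children has no basis in the text.
- *The change score biases the trial or inflates its error rate.* Over all randomisations it does neither.

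It is also fair to say that the precision gain rests on an assumed r and on equal variances, which a bounded scale may violate. The true/false argument applies to the knowledge test and does not carry over to the attitude cards.

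**Conclusion.** The point holds as a specific and inexpensive improvement. The knowledge and attitude outcomes are pre-post differences, no baseline-score adjustment is committed to, and confounders are identified only after the baseline data have been compared and tested. The cost is lost precision and sensitivity to chance imbalance among 30 schools, not bias.

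The size cannot be fixed from the article. With equal variances, the adjusted variance is 0.65 to 0.95 of the change-score variance for r from 0.3 to 0.9, with r taken at the level analysed. At the upper end the cost of estimating the slope from 30 schools takes up most of the gain. These ratios do not convert into a revised sample size, because the trial was sized on proportions.

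One minor mismatch remains: item 2 plans to compare family characteristics, but the demographic variables listed are only age, date of birth and gender.

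**What to change.** In Assessment of efficacy and Statistical analysis:

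1. State that the arm comparison of each knowledge and attitude score adjusts for the baseline value of that score. In a multilevel model, include both the child's baseline score and the school mean. In the cluster-summary analysis, use the school mean baseline score. The outcome may still be expressed as a difference.
2. Fix a short covariate list from data already held: sex, age, rural/urban location and socioeconomic level. Keep the school-level terms few, because there are only 30 schools.
3. State how this model relates to the cluster summaries in the abstract and to the risk measures in item 3, and which of them is primary.
4. Delete the parametric tests of randomisation and the later identification of confounders. Present baseline data descriptively by arm.
5. Either list the family variables to be collected or remove them from item 2.

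This needs no new data and no change to the conduct of the trial. It is more than a change of wording only at step 3, where the effect measure has to be settled.
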